### Recurrence rate

Patients who were cured will attend the second follow-up after 28 days to assess the recurrence rate. Recurrence criteria must include item (i) and either (ii) or (iii) at the same time, or item (i) alone.

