## Method/design

### Objective and design

This is a randomized, double-blind, double-dummy, parallel control of positive drug, multicentre clinical study. The study will be conducted at: the XiYuan Hospital, China Academy of Chinese Medical Sciences; the Longhua Hospital Shanghai University of Traditional Chinese Medicine; the Guangdong Provincial Hospital of Traditional Chinese Medicine; the Hubei Hospital of Traditional Chinese Medicine; the Affiliated hospital of Chengdu University of Traditional Chinese Medicine; and the Yunnan Provincial Hospital of Traditional Chinese Medicine. Ethical clearance for the trial was obtained from ethics committee of the six hospitals. Patients with acute uncomplicated lower UTI will undergo a standardized baseline evaluation before treatment, comprising detailed history taking, physical examination, and laboratory testing. All included patients are randomly divided into three groups: experimental group; control group 1; and control group 2. The experimental group receives SJT plus levofloxacin tablets (LT) placebo; control group 1 receives LT plus SJT placebo; and control group 2 receives SJT plus LT on the first five days, SJT plus LT placebo on the last two days. After seven days of treatment, the efficacy and safety of three groups will be evaluated. The first aim is to determine whether SJT can reduce the use of antibiotics (control group 2 versus control group 1, non-inferiority test); the second aim is to determine whether SJT can substitute the use of antibiotics (experimental group versus control group 1, non-inferiority test). The recurrence rate will be assessed at the 28-day follow-up after being cured to determine whether SJT can reduce the recurrence rate. The trial is conducted in accordance with the World Medical Association Declaration of Helsinki and Good Clinical Practice of Pharmaceutical Products [17, 18]. After a full explanation by the clinicians, written informed consent will be obtained from the participants before intervention [19, 20]. Strict data management and quality control will be conducted in this trial [21, 22]. This trial was registered in the Clinical Trials USA registry (registration No. NCT03658291) on 4 September 2018 and will be carried out from January 2019 to December 2019. The study design is shown in Fig. 1. The protocol follows the recommendations of the SPIRIT initiative (see Additional file 1) [23] and the trial results will be reported according to the latest version of the CONSORT statement [24].

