#### Exit criteria

Patients will leave the trial when one of the following criteria is met: (i) incorrectly included; (ii) are poorly compliant or pregnant; (iii) no medication or any follow-up records; (iv) occurrence of allergic reactions or serious adverse events (AE); (v) participants have other complications or special physiological changes during the trial; (vi) patients have been treated with other medicines during the trial; and (vii) not alleviated or the symptoms are aggravated. Participants may withdraw from the study at any time for any reason.

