## Follow-up

All included patients will be re-evaluated after seven days of treatment follow-ups as an outpatient to assess the efficacy and safety. The patients who were cured will receive the second follow-up after 28 days to assess the recurrence rate. Patients whose symptoms worsened will receive a supply of relevant medicine and a written withdrawal schedule. Assessment of study endpoints and duration of follow-up is shown in Fig. 2.

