#### Criteria of comprehensive efficacy

(i)Criteria of cure: the evaluation of clinical symptoms reached the level of cure after seven days of treatment; the value of urine leukocytes returned to the normal value; the original infected bacteria was cleared after seven days of treatment. All three criteria must be met.(ii)Criteria of effective treatment: the clinical symptoms were alleviated but did not reach the level of cure after seven days of treatment; the value of urine leukocytes was reduced but not returned to normal after seven days of treatment. Either of these criteria must be met.(iii)Criteria of invalid treatment: the clinical symptoms were not alleviated after seven days of treatment; the value of urine leukocytes was still higher than normal after seven days of treatment; the original infected bacteria were still cultured from the original infection position after seven days of treatment. All three criteria must be met.

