#### Primary outcome measure

(i)The recurrence rate of cured participants will be assessed by the symptoms of acute uncomplicated lower UTI. The assessment tools of renewed symptoms will also use the three participant self-rating scales (see Additional file 2): CSESUSI; SSST; and OABSS. If the symptoms of cured patients reappeared in the fourth week after the end of medication, it indicates the participant has relapsed.

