### Data analysis

Data analysis will be performed by professional statisticians using SPSS 22.0. Three datasets will be conducted: intention-to-treat; per-protocol set; and safety dataset. The intention-to-treat refers to the patients who have been randomized; an intentional analysis will be conducted for curative effect. The per-protocol set refers to all cases that do not violate the protocol and complete the trial; per-protocol set analysis will be conducted for curative effect. The safety dataset refers to the randomized cases that have taken a tested drug at least once with safety evaluation data after treatment. We use mean ± standard deviation (SD) for continuous variables and percentages for categorical variables. In measured indices, the independent t-test will be used for hypothesis testing of the normal variables, while the Wilcoxon rank sum test will be used for hypothesis testing of the skewed variables. The χ^2^ test will be used for hypothesis testing of the counted indices. The statistical analyses will use the two-sided hypothesis test. *P* ≤ 0.05 will be set as the significant level.

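### Recurrence is compared only among patients cured at day 7, a subset that treatment can select, so it cannot by itself show that SJT reduces recurrence

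*Protocol article*

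**What the plan says.** Under Recurrence rate, the protocol article states: "Patients who were cured will attend the second follow-up after 28 days to assess the recurrence rate". The Follow-up section agrees: all included patients are re-evaluated after seven days of treatment, but only the cured return. The outcome headed as primary for recurrence uses the same denominator: "The recurrence rate of cured participants will be assessed by the symptoms of acute uncomplicated lower UTI". The two secondary recurrence measures, by urine leukocytes and by bacteriology, are also defined on cured patients.

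The purpose is given under Objective and design and repeated in the Discussion: "The recurrence rate will be assessed at the 28-day follow-up after being cured to determine whether SJT can reduce the recurrence rate".

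Cure is judged after treatment. The comprehensive definition requires symptoms, leukocytes and culture all to have resolved ("the original infected bacteria was cleared after seven days of treatment. All three criteria must be met"), whereas the effective-rate primary outcome describes cure by symptoms alone. One exit criterion is "not alleviated or the symptoms are aggravated", so patients who do not respond leave the trial and are never assessed for recurrence. No recurrence or sustained-cure outcome over all randomised patients is given. The test named for counts under Data analysis is a χ² test.

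**The concern.** The question is causal: does SJT lower recurrence? The comparison meant to answer it is made in groups formed after randomisation by the outcome of treatment. An arm that clears mainly the easy infections sends mainly low-risk patients to the second follow-up, and its recurrence rate can be low for that reason alone.

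Differing cure rates are a realistic possibility here. By Table 1 the experimental group receives no active levofloxacin, while the inclusion criteria call for infections sensitive to levofloxacin, and the protocol itself treats substitution for the antibiotic as an open question. The trial could therefore credit SJT with preventing recurrence when fewer of its patients end up cured and still well. It could also do the reverse and hide a benefit.

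**Working it through.** The protocol article gives no expected recurrence rate and no sample size for recurrence, so there is no figure of the plan to reproduce. The check asks whether the planned comparison can show a difference when treatment has no effect on relapse.

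**Model.** Two kinds of patient, easy and hard to cure. Relapse risk after cure depends only on the kind of patient and is the same in every arm, so the true effect on relapse is nil.

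- Cured = 0.6 × (easy cure) + 0.4 × (hard cure)
- Recurrent = 0.6 × (easy cure) × (easy relapse) + 0.4 × (hard cure) × (hard relapse)
- Recurrence among the cured = recurrent / cured
- Sustained cure among all randomised = cured − recurrent

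**Inputs.** All are assumed; none is in the documents. The mix is 60% easy and 40% hard. Relapse once cured is 5% (easy) and 30% (hard). Levofloxacin cures 95% of easy and 80% of hard cases; SJT cures 90% and 30%.

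**Levofloxacin.**
- Cured: 0.6 × 0.95 + 0.4 × 0.80 = 0.57 + 0.32 = 0.89
- Recurrent: 0.57 × 0.05 + 0.32 × 0.30 = 0.0285 + 0.0960 = 0.1245
- Among the cured: 0.1245 / 0.89 = 14.0%
- Sustained cure: 0.89 − 0.1245 = 76.55%

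**SJT.**
- Cured: 0.6 × 0.90 + 0.4 × 0.30 = 0.54 + 0.12 = 0.66
- Recurrent: 0.54 × 0.05 + 0.12 × 0.30 = 0.027 + 0.036 = 0.063
- Among the cured: 0.063 / 0.66 = 9.5%
- Sustained cure: 0.66 − 0.063 = 59.7%

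The risk ratio among the cured is 0.0955 / 0.1399 = 0.68 in favour of SJT, although relapse is unaffected. Sustained cure ranks the arms the other way.

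**Range when SJT cures fewer hard cases.** Ratio among the cured, other inputs as above:

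| Hard-case relapse | SJT hard-case cure 30% | 50% | 65% |
|---|---|---|---|
| 15% | 0.79 | 0.90 | 0.96 |
| 30% | 0.68 | 0.84 | 0.94 |
| 45% | 0.63 | 0.82 | 0.93 |

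**Direction is not fixed.** With hard-case relapse at 30% and the same levofloxacin arm (14.0%):

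- Comparator arm cures 90% easy, 80% hard: 0.123 / 0.86 = 14.3%, ratio 1.02.
- Cures 70% easy, 80% hard: 0.117 / 0.74 = 15.8%, ratio 1.13.
- Cures 95% easy, 90% hard, as SJT plus levofloxacin might: 0.1365 / 0.93 = 14.7%, ratio 1.05.

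If relapse risk is the same in easy and hard cases, the ratio is 1.00 whatever the cure rates.

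**False significance.** Trials were simulated with 84 patients per arm (252 / 3) and an uncorrected χ² test at two-sided 0.05 among the cured. The nominal rate of false significance favouring SJT is 2.5%. It is about 11% in the 0.68 scenario, and about 3% to 4% when SJT cures 65% of hard cases (overall cure 80% versus 89%). A separate set of assumptions used hard-case cure of 70% versus 20%, easy-case cure of 90% in both arms, 40–50% hard cases, and relapse of 5–10% (easy) and 30–40% (hard). It gave 8.9% to 23.0%.

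**The case against.** Recurrence can be observed only after cure, so a rate among the cured is a legitimate description. That stands, and the rate should be kept. What does not follow is a between-arm causal claim resting on it alone.

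The Sample size section makes the effective rate the main outcome measure, and the two numbered aims are non-inferiority comparisons. Recurrence is a further question with no stated hypothesis or power. This also stands: the flaw leaves both aims intact and limits the wording of one further result.

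The larger false effects need a large cure deficit (66% versus 89% for the ratio of 0.68), which the trial's own efficacy comparison would display. At 80% versus 89% the ratio is only 0.93 to 0.96. This is fair, and it is why the size must be given as a range under assumptions.

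Two stronger readings are tempting. A reader might infer that the bias always favours SJT. The documents do not support that: the table above has this direction because every cell has SJT curing fewer hard cases and hard cases relapsing more often, and other inputs reverse it. A reader might also infer that a rate among the cured contradicts the intention-to-treat definition. It does not, because Data analysis ties that set to another purpose: "The intention-to-treat refers to the patients who have been randomized; an intentional analysis will be conducted for curative effect". Recurrence is not mentioned there, so there is no conflict to reconcile.

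Finally, sustained cure cannot isolate relapse: an arm could win on cure alone. That is true, and it is why the fix must restrict the conclusion as well as add an analysis.

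**Conclusion.** The concern holds as a point that should be fixed. The protocol article states both the denominator (the cured) and the inference (whether SJT reduces recurrence), so this is more than detail left to an analysis plan. Followed as written, the recurrence comparison is not protected by randomisation.

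Whether it is biased in fact depends on two conditions that the documents do not settle: that arms differ in which patients they cure, and that relapse risk differs between those patients. The loss of randomised comparability does not depend on any assumed figure; the ratios do. The comparison of control group 2 with control group 1 is open to the same problem, though a large cure deficit is less obvious there because that group also receives five days of levofloxacin.

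**What to change.** In the Recurrence rate and Data analysis sections:

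- Add, as the randomised comparison for the recurrence objective, sustained cure: cured at day 7 and no recurrence by the second follow-up, in all randomised patients.
- Name one definition of cure for it, either the symptom-based one or the three-part comprehensive one.
- Compare each SJT-containing arm with control group 1, as a difference with a 95% confidence interval.
- Count patients not cured or withdrawn as failures. Count cured patients who miss the second visit as failures too, with a sensitivity analysis for that choice.
- Keep recurrence among the cured as a descriptive rate, and state that it will not alone support a conclusion that SJT reduces recurrence. Word a difference in sustained cure as sustained cure, not as reduced relapse.

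The cost is about a paragraph of text. No extra visit is needed, because patients not cured at day 7 already count as failures. The downside is that sustained cure mixes cure with relapse and cannot separate the two.

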**Methods/design:**

In this study, a randomized, double-blind, double-dummy, parallel control of positive drug, multicenter clinical study will be established. A total of 252 patients with acute uncomplicated lower UTI (syndrome of dampness-heat in the lower jiao) will be randomly allocated in the ratio of 1:1:1 to three groups: experimental group; control group 1; and control group 2. The experimental group receives Sanjin tablets plus levofloxacin tablets (LT) placebo; the control group 1 receives LT plus SJT placebo; and the control group 2 receives SJT plus LT on the first five days, SJT plus LT placebo on the last two days. Each group will be treated for seven days and followed-up 1–2 times. The primary outcome measures of effective rate and recurrence rate are symptoms. Secondary outcome measures of effective rate and recurrence rate are the urine leukocytes, bacteriology examination, and safety assessment. Outcomes will be assessed at baseline and after treatment.

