#### Secondary outcome measures

(ii)The recurrence rate of cured participants will be assessed by urine leukocytes. If the urine leukocyte value of cured patients increased again in the fourth week after the end of medication, it indicates the participant has relapsed.(iii)The recurrence rate of cured participants will be assessed by bacteriological examination. If the urine culture of cured patients indicated that the original urinary tract pathogen is positive again in the fourth week after the end of medication, it indicates the participant has relapsed.

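### Recurrence, a primary outcome, is assessed only in patients whom treatment has cured, so a between-arm difference is not a randomised comparison; its definitions also need reconciling

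*Protocol article*

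**What the plan says.** The abstract (Methods/design) gives recurrence primary status: "The primary outcome measures of effective rate and recurrence rate are symptoms". Objective and design states a comparative purpose: "The recurrence rate will be assessed at the 28-day follow-up after being cured to determine whether SJT can reduce the recurrence rate".

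The population is restricted in several places. Follow-up says "The patients who were cured will receive the second follow-up after 28 days to assess the recurrence rate", and the Recurrence rate section repeats it: "Patients who were cured will attend the second follow-up after 28 days to assess the recurrence rate". The primary measure in that section has the same denominator: "The recurrence rate of cured participants will be assessed by the symptoms of acute uncomplicated lower UTI".

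The event is defined by the rule "Recurrence criteria must include item (i) and either (ii) or (iii) at the same time, or item (i) alone". Item (i) is met "If the symptoms of cured patients reappeared in the fourth week after the end of medication". Under the secondary measures, item (ii) counts as relapse by itself "If the urine leukocyte value of cured patients increased again in the fourth week after the end of medication", and item (iii), a renewed positive culture, is worded in the same way.

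Data analysis ties the intention-to-treat set to curative effect. It mentions no all-randomised analysis of recurrence.

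**The concern.** Cure at day 7 happens after randomisation and is affected by treatment. If one arm cures mainly patients who are also less likely to relapse, its cured patients will show fewer recurrences even if the drug does nothing to recurrence. Unequal cure is foreseeable here: one arm receives no antibiotic, the enrolled infections are meant to be levofloxacin-sensitive, and the non-inferiority questions are asked because SJT may cure fewer patients. A statement that SJT reduces recurrence would then lack the protection of randomisation, although the outcome is called primary.

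The choice of population is written into the article, so it is not a detail left to an unseen analysis plan. The loose definitions add to the problem, because both the denominator and the events counted depend on which paragraph is followed.

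**Working it through.** **Inputs.** The article gives no recurrence rate, cure rate or power for recurrence, so there is no figure of its own to reproduce. The 77.14% under Sample size is an effective rate for SJT, not a cure rate. Every rate below is an assumption chosen to show the mechanism.

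**1. The denominator.** Take a share π of easy and 1 − π of hard patients, with cure probabilities c_e and c_h. Relapse risks r_e and r_h are the same in both arms, so there is no drug effect on relapse.

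- Cured: C = π·c_e + (1 − π)·c_h
- Recurrence among the cured: R = [π·c_e·r_e + (1 − π)·c_h·r_h] / C
- Cured and still well, of all randomised: S = C(1 − R)
- With w the share of hard patients among the cured: R_SJT − R_LT = (w_SJT − w_LT)(r_h − r_e)

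Scenario A in full (π = 0.6, r_e = 10%, r_h = 40%):

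- LT, cure 95%/58%: C = 0.570 + 0.232 = 0.802; R = (0.057 + 0.0928)/0.802 = 18.7%; S = 65.2%.
- SJT, cure 90%/15%: C = 0.540 + 0.060 = 0.600; R = (0.054 + 0.024)/0.600 = 13.0%; S = 52.2%.
- Check: w is 0.232/0.802 = 0.289 on LT and 0.060/0.600 = 0.100 on SJT; (0.100 − 0.289) × 0.30 = −0.057.

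Scenarios B to E use π = 0.5. Each pair is LT v SJT.

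| | Cure easy/hard, LT v SJT | Relapse easy/hard | C | R among cured | Difference in R | S, all randomised | Difference in S |
|---|---|---|---|---|---|---|---|
| A | 95/58 v 90/15 | 10/40 | 80.2 v 60.0 | 18.7 v 13.0 | −5.7 | 65.22 v 52.20 | −13.02 |
| B | 95/75 v 90/40 | 5/25 | 85 v 65 | 13.8 v 11.2 | −2.7 | 73.25 v 57.75 | −15.50 |
| C | 95/75 v 85/25 | 10/40 | 85 v 55 | 23.2 v 16.8 | −6.4 | 65.25 v 45.75 | −19.50 |
| D | 95/85 v 90/64 | 5/25 | 90 v 77 | 14.4 v 13.3 | −1.1 | 77.00 v 66.75 | −10.25 |
| E | 90/64 v 90/64 | 10/40 | 77 v 77 | 22.5 v 22.5 | 0 | 59.70 v 59.70 | 0 |

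In A to D the arm that cures fewer patients looks better on recurrence among the cured and worse on sustained cure. The formula shows that the sign follows the mix of patients cured. If an arm cured a larger share of hard patients, the bias would run against it.

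**2. The rule.** There are eight combinations of items (i), (ii) and (iii). In the four with (i) present, the final clause is met whatever the laboratory shows. In the four with (i) absent, both clauses fail. The rule therefore equals (i). In three of the four combinations without symptoms (leukocytes raised, culture positive, or both), the secondary measures nevertheless call the patient relapsed.

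**3. Who is cured.** Under Effective rate, the primary measure calls a patient cured when symptoms have gone. The secondary measure calls a patient cured when urine leukocytes are normal. Criteria of comprehensive efficacy requires symptoms, leukocytes and bacterial clearance together. The recurrence text does not say which of these decides who is followed and counted.

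**4. The window.** Items (i) to (iii) all refer to the fourth week after medication ends. A recurrence in weeks 1 to 3 that has resolved by then does not fit that wording. Under Exit criteria (vi), patients given other medicines during the trial leave it. If that criterion runs to the 28-day visit, a treated early recurrence is withdrawn. On either route it can be lost from the count.

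**The case against.** **The size is invented, and other results would warn the reader.** This is fair as to size. In scenario A the analysis of cure would show SJT about 20 points worse, so a recurrence claim would not stand alone. With 252/3 = 84 per arm, about 67 and 50 patients would be cured; the standard error is √(0.187 × 0.813/67 + 0.13 × 0.87/50) ≈ 0.067, and the 5.7-point artefact is about 0.85 standard errors, so it would usually not reach significance. Selection may also be weaker in control group 2 versus control group 1, where both arms receive levofloxacin. None of this makes the comparison randomised.

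**The rule misclassifies nobody on the primary.** This stands. The rule reduces to item (i), which is already the primary measure. A reader might infer that a symptom-free patient with a positive culture is both relapsed and not relapsed. The article does not force that reading, because the laboratory items sit under secondary measures and can be taken as separate outcomes. What remains is wording to reconcile.

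**The three-part cure is probably meant.** Leukocytes rising again and a culture turning positive again presuppose that both had normalised, and the comprehensive criteria come just before the recurrence section. That is plausible, but it is not stated, and the primary measure also uses the word cured.

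**Early recurrences are not said to be scored as relapse-free.** Correct. A reader might infer that scoring from the fourth-week wording, but the article does not state it, and the exit criterion may apply instead. The supportable point is that such events can be missed.

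**Recurrence is not what the trial was sized for.** Sample size names the effective rate as the main outcome, and the numbered aims concern antibiotic use. The abstract and the Recurrence rate section still label recurrence primary.

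**Conclusion.** The point holds. The article fixes a denominator selected by treatment for an outcome that it calls primary and intends to use comparatively, so a difference in recurrence among the cured cannot by itself be attributed to SJT. The illustrative artefact is 1.1 to 6.4 points. It rests on assumed cure and relapse rates and on relapse risk being linked to how hard a patient is to cure. It is zero if both arms cure the same patients, and its direction is not fixed. A reader might go further and infer that a lower SJT recurrence rate would have to be spurious; the article gives no rates that would support that.

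Three lesser defects also hold: three unreconciled meanings of cured, a recurrence rule that does not match the stand-alone laboratory relapse, and a window that can miss events in weeks 1 to 3.

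**What to change.** - **Comparison.** Base any between-arm claim on being cured at day 7 and recurrence-free through the 28-day visit, in all randomised patients. Count uncured patients as not achieving it; they need no extra visit. Keep recurrence among the cured as a descriptive result with no causal claim.
- **Cured.** Name one definition for this endpoint. The symptom cure would match the primary measure, with the comprehensive cure as a sensitivity analysis.
- **Recurrence.** State primary recurrence as item (i). Keep leukocyte and culture recurrence as separately labelled secondary measures, and reword the rule in the Recurrence rate section to agree with them.
- **Window.** Count symptomatic recurrence at any time from the end of medication to the 28-day visit, using a history question at that visit. In the analysis, count patients who leave under Exit criteria (vi) for a treated recurrence as recurrences.

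The cost is a change to definitions and analysis wording plus one question at an existing visit. It should be settled before unblinding. The drawback is that the composite is partly driven by day-7 cure: it answers whether patients are cured and stay well, not whether SJT lowers recurrence after cure alone, and the report should say so.
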